## Abstract

**Background:**

The main hypothesis of this study is that oral heme iron polypeptide (HIP; Proferrin^® ^ES) administration will more effectively augment iron stores in erythropoietic stimulatory agent (ESA)-treated peritoneal dialysis (PD) patients than conventional oral iron supplementation (Ferrogradumet^®^).

**Methods:**

Inclusion criteria are peritoneal dialysis patients treated with darbepoietin alpha (DPO; Aranesp^®^, Amgen) for ≥ 1 month. Patients will be randomized 1:1 to receive either slow-release ferrous sulphate (1 tablet twice daily; control) or HIP (1 tablet twice daily) for a period of 6 months. The study will follow an open-label design but outcome assessors will be blinded to study treatment. During the 6-month study period, haemoglobin levels will be measured monthly and iron studies (including transferring saturation [TSAT] measurements) will be performed bi-monthly. The primary outcome measure will be the difference in TSAT levels between the 2 groups at the end of the 6 month study period, adjusted for baseline values using analysis of covariance (ANCOVA). Secondary outcome measures will include serum ferritin concentration, haemoglobin level, DPO dosage, Key's index (DPO dosage divided by haemoglobin concentration), and occurrence of adverse events (especially gastrointestinal adverse events).

**Discussion:**

This investigator-initiated multicentre study has been designed to provide evidence to help nephrologists and their peritoneal dialysis patients determine whether HIP administration more effectively augments iron stores in ESP-treated PD patients than conventional oral iron supplementation.

**Trial Registration:**

Australia New Zealand Clinical Trials Registry number ACTRN12609000432213.

## Background

Anemia develops early in the course of chronic kidney disease (CKD) and is nearly universal in patients with CKD stage 5 [1]. The severity of anemia is related to both the degree of loss of glomerular filtration rate (GFR) and the cause of kidney disease [2]. The development of erythropoietic stimulatory agents (ESA), such as recombinant human erythropoietin (EPO) and darbepoietin alpha (DPO), has resulted in substantial health benefits for patients with end-stage renal failure, including improved quality of life, reduced blood transfusion requirements, decreased left ventricular mass, diminished sleep disturbance and enhanced exercise capacity [3,4]. Unfortunately, a considerable proportion of such patients exhibit a suboptimal haematologic response to ESA, which in most cases is due to inadequate iron supply to the erythron [1]. Concomitant iron supplementation is therefore required in as many as 90% of EPO-treated individuals [5].

In haemodialysis populations, several investigations, including a randomised controlled trial, have consistently demonstrated that intravenous iron supplementation is superior to oral iron replacement with respect to enhancing body iron stores, augmenting haemoglobin levels and reducing EPO requirements [5-7]. However, there is ongoing controversy as to whether iron supplementation is best administered orally or intravenously in peritoneal dialysis (PD) patients (and pre-dialysis patients), in whom repeated intravenous cannulation is logistically more difficult. Our group recently performed a cross-over trial of oral iron versus 2-monthly intravenous iron infusions in 28 PD patients and demonstrated that IV iron supplementation was associated with a much lower incidence of gastrointestinal disturbances (11% versus 46%, p < 0.05) and superior haemoglobin levels and body iron stores, but exceeded the cost of oral iron treatment by 6.5-fold [8]. Other investigators have similarly demonstrated that oral iron supplements are unable to maintain adequate iron stores in PD patients over medium-to-long term periods [5], principally because of poor compliance, gastrointestinal side effects, suboptimal gastrointestinal absorption of iron (particularly in the presence of an acute phase response and high ferritin levels), and medication costs [9]. In spite of this evidence, many authors [10-12] and clinical practice guidelines [13-15] have recommended oral iron supplementation for PD patients in the first instance, because of its greater simplicity, lower cost and avoidance of the need for repeated intravenous cannulation.

The development of an oral iron supplement which safely, cheaply and more effectively maintains iron stores and haemoglobin levels in ESP-treated PD patients would therefore be of considerable clinical utility. Preliminary evidence suggests that heme iron polypeptide (HIP) may represent such a promising, novel, therapeutic strategy. HIP is produced by hydrolysis of bovine haemoglobin resulting in a highly soluble heme moiety that contains more than 1% iron. Since heme is absorbed via a different receptor to that utilised by nonheme (ionic) iron [16,17], the absorption kinetics and gastrointestinal side effect profiles of HIP and ionic iron are dissimilar. Administration of HIP to 14 healthy subjects was associated with fewer side effects and significantly higher bioavailability compared with nonheme iron [18]. Specifically, the study demonstrated that HIP increased serum iron levels 23 times greater than ferrous fumarate on a milligram-per-milligram basis. One of the possible reasons for why heme iron is more bioavailable than ionic iron is thought to be due the fact that the gastrointestinal absorption of heme iron is far less affected by dietary constituents, such as polyphenolic tannins, phytates, soy and dairy products [18]. Hallberg et al [19] also demonstrated that the absorption of heme iron may be more than 10 times greater than that of iron salts in subjects with serum ferritin levels greater than 400 ng/mL (898 pmol/L). Moreover, the gastrointestinal absorption of both heme and non-heme iron is significantly increased by stimulation with ESA [20]. Recently, Nissenson et al [21] performed an open-label, pre-test/post-test trial of HIP (1 tablet tds) administered in lieu of intravenous iron supplementation to 37 ESA-treated haemodialysis patients over a 6 month period. Although 4 (11%) of 37 patients dropped out due to gastrointestinal intolerance (n = 3) or insufficient iron supplementation (n = 1) and 5 patients (14%) were excluded due to unrelated complications or protocol violation, HIP successfully replaced IV therapy in the majority of patients, resulting in maintenance of haematocrit targets and iron stores and significant improvement in EPO efficiency (mean EPO dose/haemoglobin levels fell from 1270 to 1023 U.g/mo/dL, p = 0.04). However, the results of this study were significantly limited by its open label non-randomised design, potential for co-intervention and observer biases, high drop-out rate (25% over 6 months) and failure to analyse on an intention to treat basis. There have been no other trials of HIP in chronic kidney disease patients (including PD patients).

## Methods/Design

### Objectives

The primary objective is to determine whether oral HIP administration (two tablets nocte per os, equivalent to 24 mg elemental iron per day) results in significantly higher transferrin saturation (TSAT) values in PD patients treated with DPO at 6 months compared with conventional oral slow-release ferrous sulphate supplementation (two tablets nocte per os, equivalent to 210 mg elemental iron per day).

The secondary objectives will be to determine whether oral HIP administration (two tablets nocte per os, equivalent to 24 mg elemental iron per day) to DPO-treated PD patients over 6 months results in

a) an increase in serum ferritin concentrations;

b) an increase in haemoglobin levels;

c) a reduction in the prescribed dosages of DPO (Aranesp^®^, Amgen);

d) a reduction in Key's index (DPO dosage divided by haemoglobin concentration); and,

e) a reduction in significant side effects (especially gastrointestinal side effects).

Ethics approval for the **HEM**e iron polypeptide **A**gainst **T**reatment with **O**ral **C**ontrolled **R**elease **I**ron **T**ablets trial (HEMATOCRIT trial) has been obtained from the local Institutional Ethics Committee in all participating centres prior to study initiation and patient enrolment. The study will be performed in accordance with the 2000 Edinburgh, Scotland Revision of the Declaration of Helsinki, the National Health and Medical Research Committee (NHMRC) Statement on Human Experimentation, Joint NHMRC/AVCC Statement and Guidelines on Research Practice, applicable ICH guidelines and the Therapeutic Goods Administration (TGA) – Note for guidance on good clinical practice (CPMP/ICH/135/95) annotated with TGA.

### Participants

The study population includes adult (18 years or over) patients willing to give informed consent who have been on PD for > 1 month and receiving DPO for > 1 month. Patients will be recruited by local investigators from PD units at three Australian centres. The clinical and demographic characteristics of this population are comparable to those reported for the Australian and New Zealand PD population by the ANZDATA Registry. This, along with the multicentre nature of the trial will enhance its generalisability.

Exclusion criteria include:

1. Patients with a history of psychological illness or condition which interferes with their ability to understand or comply with the requirements of the study.

2. Pregnancy or breast-feeding.

3. Known hypersensitivity to, or intolerance of, oral iron, HIP or DPO.

4. Active peptic ulcer disease.

5. Vitamin B12 or folate deficiency.

6. Recent (within 1 month) acute infection.

7. Parathyroid hormone level > 100 pmol/L.

8. Serum aluminium > 2 μmol/L.

9. Presence of systemic haematological disease (including antibody-mediated pure red cell aplasia) or known haemoglobinopathy

10. Major surgery, infection, acute myocardial infarction or malignancy within the last 3 months.

11. Intravenous iron therapy, vitamin C therapy, melatonin treatment, androgen therapy or blood transfusion within the previous month.

12. Serum ferritin ≥ 500 μg/mL or transferrin saturation (TSAT) ≥ 50%.

13. Religious or other objection to consuming product prepared from bovine blood.

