### Sample size calculations

Prospective power calculations indicate that the study will have adequate statistical power (80% probability) to detect a clinically significant increase in TSAT of 7%, assuming α = 0.05 and a population standard deviation of 8%, if 44 patients were recruited in the study (22 in each group). Allowing for a 15% drop-out rate over 6 months using the adjustment formula of 1/[1 - drop-out rate] ^2^, we aim to recruit a total of 60 patients (30 in each group). We anticipate that a recruitment period of 18 months will be required. The assumptions for these power calculations were based on a previous randomised controlled trial of oral versus intravenous iron supplementation in PD patients [8], in which the baseline values were 107 ± 3 g/L for haemoglobin, 24.2 ± 1.7% for transferrin saturation and 323 ± 46 μg/L for serum ferritin concentration. Based on these assumptions, we estimate the power of the study for secondary outcome measures to be 77% for serum ferritin (δ 150 μg/mL, σ 180 μg/mL), 62% for haemoglobin (δ 7 g/L, σ 10 g/L), 22% for DPO divided by haemoglobin (δ 0.00075 μg.L/kg.g/week, σ 0.002 μg.L/kg.g/week) and 93% for the occurrence of gastrointestinal events (HIP 8% vs ferrous sulphate 46%).

The assumptions used for the power calculations are conservative and based on our previous study in 28 PD patients [22] and that of Nissenson et al in 37 haemodialysis patients ^1^. Because of power considerations and the relatively short duration of the study, no interim analysis is planned.

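### The ferritin ceiling in exclusion criterion 12 is printed on a scale 1,000 times that of the baseline ferritin, so as written the ferritin limb excludes nobody

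*Protocol article*

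**What the plan says.** All places are in the protocol article.

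- **Participants, exclusion criterion 12:** "Serum ferritin ≥ 500 μg/mL or transferrin saturation (TSAT) ≥ 50"%. The two limbs are joined by *or*, so either one alone excludes.
- **Sample size calculations, baseline in the trial used for planning:** "323 ± 46 μg/L for serum ferritin concentration". The ± is not labelled as a standard deviation or a standard error.
- **Sample size calculations, secondary outcomes:** power of "77% for serum ferritin (δ 150 μg/mL, σ 180 μg/mL"). The unit is again μg/mL, in the sentence directly after the μg/L baseline.
- **Background, cited absorption study:** "serum ferritin levels greater than 400 ng/mL (898 pmol/L").
- **Participants, criterion 6:** "Recent (within 1 month) acute infection".
- **Participants, criterion 10:** "Major surgery, infection, acute myocardial infarction or malignancy within the last 3 months".

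**The concern.** The article states ferritin in three units. Two of them, μg/L and ng/mL, are numerically the same. The third, μg/mL, is 1,000 times larger, and it is the one attached to the eligibility threshold. A ceiling three orders of magnitude above the planning baseline cannot screen anyone out.

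The article's own reasoning makes ferritin at entry relevant to the treatment comparison. The Background reports that heme iron may be absorbed more than 10 times better than iron salts when ferritin is above 400 ng/mL, and lists high ferritin among the reasons why oral iron is poorly absorbed. Who enters at the upper end of ferritin therefore bears on the expected contrast between arms, and serum ferritin is also a secondary outcome.

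A smaller question concerns infection, which appears in two exclusion criteria with different windows and different qualifiers. The Background names an acute phase response as another cause of poor oral iron absorption, so infection history is relevant to the iron endpoints.

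**Working it through.** **1. The plan's own ferritin power figure**

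Inputs from Sample size calculations: δ = 150, σ = 180, 22 per group, α = 0.05. Sidedness is not stated; two-sided is assumed.

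- Standardised difference: δ/σ = 150/180 = 0.833.
- Noncentrality: 0.833 × √(22/2) = 2.76, with 42 degrees of freedom.
- Power from the noncentral t: 77.0%. The normal approximation gives 78.9%.

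The stated 77% is reproduced. Only δ/σ enters the formula, so the result is the same in μg/mL and in μg/L.

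**2. Unit conversion of the ceiling**

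1 μg/mL = 1,000 μg/L = 1,000 ng/mL.

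| Quantity | As printed | In μg/L |
|---|---|---|
| Criterion 12 ceiling | 500 μg/mL | 500,000 |
| Planning baseline mean | 323 μg/L | 323 |
| Level cited in Background | 400 ng/mL | 400 |
| Ferritin δ | 150 μg/mL | 150,000 |

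- Ceiling against baseline mean: 500,000/323 = 1,548.
- Ceiling against the Background level: 500,000/400 = 1,250.
- δ against baseline mean: 150,000/323 = 464. This shows that the printed δ cannot be on the same scale as the baseline.
- The number 500 on the μg/L scale would be 500/323 = 1.5 times the baseline mean.

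**3. Share of patients at or above the ceiling**

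Assumption: ferritin is normal with mean 323 μg/L. The SD is uncertain, so three values are shown. The third takes ± 46 as a standard error with the 28 patients that the Background gives for the planning trial: 46 × √28 = 243.

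| SD (μg/L) | Source | z at 500 μg/L | Share above 500 μg/L | z at 500,000 μg/L (as printed) |
|---|---|---|---|---|
| 46 | ± 46 read as SD | 177/46 = 3.85 | 0.006% | about 10,860 |
| 180 | planning σ, taken in μg/L | 177/180 = 0.98 | 16% | about 2,780 |
| 243 | ± 46 read as standard error | 177/243 = 0.73 | 23% | about 2,050 |

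As printed, the ceiling lies more than 2,000 SDs above the mean in every row, so the share excluded by the ferritin limb is effectively zero.

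**4. Infection windows**

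Each exclusion criterion is sufficient on its own. If infection in criterion 10 carries no qualifier, criteria 6 and 10 together exclude any infection in the last 3 months, and criterion 6 adds nothing. If the word *Major* in criterion 10 also governs infection, there are two tiers: major infection within 3 months and any acute infection within 1 month. Both readings can be applied, but they enrol different patients. One example is a minor infection 2 months before screening.

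**The case against.** The best defence is that this is a slip in a unit which any nephrologist would recognise, because the Background and the baseline figure make the working scale plain. Nothing in the article suggests that a site applied a limit of 500,000 μg/L. This is a fair limit on the practical consequence. It does not remove the fault: the line is an eligibility threshold, the same unit recurs for δ and σ, and the article does not show what the full protocol or screening form prints.

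Four further points for the defence stand:

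- **TSAT limb.** A reader might infer that no patient with high iron stores is screened out. That does not follow, because anyone at or above the TSAT limit is still excluded.
- **Power.** A reader might infer that the μg/mL unit undermines the ferritin power. It does not, because the unit cancels.
- **Share affected.** A reader might take 16% to 23% as a firm estimate. It depends on the SD, and falls to about 0.006% if ± 46 is an SD. The planning SDs (180 for ferritin, 8% for TSAT) lie closer to the printed ± values multiplied by √28 (243 and 9.0%) than to those values themselves (46 and 1.7%), so the standard-error reading fits better, but the article does not settle it. The normal model is also rough: with mean 323 and SD 243 it puts about 9% of patients below zero.
- **Infection.** A reader might infer that criteria 6 and 10 contradict each other or cannot be applied. They can be applied, since a patient excluded by one is excluded. Inconsistent use across the three centres is possible, but nothing in the article shows it.

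**Conclusion.** The concern holds for the ferritin limb of criterion 12. As printed, the threshold is 1,000 times the scale of the baseline and Background ferritin values, about 1,548 times the planning mean, and excludes nobody. This conclusion needs only the unit conversion.

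If 500 was intended on the μg/L scale, the share of otherwise eligible patients at stake lies between about 0.006% and 23%. That range assumes a normal distribution, a trial population resembling the planning trial, and one of three readings of the SD. The TSAT limb would remove some of these patients in any case; how many cannot be worked out from the article. No sample size or power figure changes.

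The article does not support the stronger inference that patients with high ferritin were in fact enrolled unchecked, or that there is a demonstrated safety problem, because it does not show how sites screened. The infection windows are a minor ambiguity of wording.

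**What to change.** Check the ferritin unit in criterion 12, and in the δ and σ of the Sample size calculations section, against the full protocol and the screening form used at the sites. Then state threshold, baseline, δ and σ in one unit. While doing so, label the ± values of the planning trial as SD or standard error.

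Reconcile criteria 6 and 10 so that it is clear whether the 3-month window covers any infection or only major infection, and whether criterion 6 is meant to add anything. Which ferritin threshold and which infection window are right is for the trial's investigators and is not proposed here.

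The cost is a wording correction and a check of one form, with no extra patients and no change to the power calculations. If the screening form carries the same unit, the sites need to be told, and the ferritin values of patients already enrolled should be listed against the reconciled threshold.

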### Study design

The study is a prospective, open-label, randomised controlled trial. Patients will be randomised to one of two treatment groups in equal proportion (Figure 1). To ensure adequate concealment of allocation, the randomisation will be performed using sequentially numbered, opaque, sealed envelopes, stratified for the presence or absence of a TSAT ≤ 20%. The sequence of interventions was obtained from a computer-generated random number list in permuted blocks provided through the Australasian Kidney Trials (AKTN) network.

**Figure 1 F1:**
[figure not shown]
**Trial schema**.

### Experimental Intervention

HIP (Proferrin^®^ES, Colorado Biolabs, USA) is approved for use as a dietary/nutritional supplement in Canada and the United States of America. The usual dose is 1 tablet (equivalent to 12 mg elemental iron) taken twice or thrice daily, either with or without food. The side effects reported with HIP are similar to those associated with conventional oral iron preparations and include nausea, vomiting and constipation. However, trials in healthy individuals [18] and in haemodialysis patients [21] suggest that the incidence of such adverse drug reactions is relatively low, possibly due to the different absorption characteristics of heme versus non-heme iron. For example, in a study of 37 haemodialysis patients receiving HIP for 6 months, constipation occurred in 3 (8%) patients and was the only observed adverse effect of the agent. The dose of HIP used in that investigation (3 tablets per day) was 50% higher than that proposed in the present study (2 tablets per day). There are no other published data concerning the side effect profile of HIP in end-stage renal failure patients. Concern has previously been expressed about the possibility of transmission of bovine spongiform encephalopathy (BSE) through the consumption of bovine tissue [21]. Currently, HIP is manufactured from red blood cells of cows of American origin, and both the US Department of Agriculture and Food and Drug Administration (FDA) currently maintain that the United States is free of BSE. In addition, the putative infectious agents for BSE, conformationally shifted neuronal membrane copper-binding proteins called prions, usually are not found in blood [21]. Thus, the risk of BSE from taking HIP is negligible.

### Control Intervention

Slow-release ferrous sulphate (Ferrogradumet^®^, Abbott, Sydney, Australia) is registered in Australia for use as an oral iron supplement and is one of the most common supplements prescribed in dialysis populations. The usual recommended dose is 2 to 3 tablets a day (equivalent to 210 to 315 mg of elemental iron per day). However, gastrointestinal side effects (especially constipation) usually limit the maximum dosage in end-stage renal failure patients to 2 tablets per day (the dose proposed in the current study). The side effects reported with Ferro-Gradumet are similar to those associated with other conventional oral iron preparations, although the incidence may be lower due to the controlled release nature of the formulation. They are as follows: nausea, vomiting, abdominal pain or discomfort, blackening of stools, diarrhoea and constipation. In a study of 28 PD patients at Princess Alexandra Hospital, oral Ferrogradumet^® ^administration in a dose of 2 tablets per day for 4 months was associated with significant gastrointestinal side effects in 46% of patients (constipation 38%, nausea 19%, abdominal pain 4%). A randomised, placebo-controlled trial of oral ferrous sulphate in 32 consecutive iron-replete dialysis patients similarly revealed significant gastrointestinal side effects in 50% of subjects [22]. Ferrous sulphate absorption is significantly inhibited by concomitant food and phosphate binder medications. Consequently, subjects participating in the present trial will be instructed to take their study medications on an empty stomach and at least 2 hours apart from phosphate binder ingestion.

### Concurrent Treatments

Vitamin B and folic acid supplementation are permitted. Vitamin C supplementation, melatonin and androgen therapy are prohibited during the study period.

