### Blinding

Blinding is not able to be performed as it is not possible to formulate identical-appearing preparations of HIP and slow-release iron. The controlled release iron tablets are too large to enclose in capsules and cannot be cut or ground. Consequently, the study will follow an open label design. An individual patient's participation in the study will cease at the end of the 6 month study period. If, before this time, the patient experiences severe anaemia (<65 g/L), symptomatic anaemia or the patient's attending physician believes that additional therapy is required (eg blood transfusion), they will be considered to have reached an end-point and will be withdrawn from study medication, but will still be followed up, with outcomes measured.

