### Procedures

Patients will take 2 tablets (HIP or ferrous sulphate) nocte for a period of 6 months. They will be instructed to take their study medications on an empty stomach and at least 2 hours apart from phosphate binder ingestion. At the time of inclusion in the study, demographic and clinical data will be recorded. All patients will be allowed their usual diet during the study period. DPO dosages will modified according to unit protocols, based on haemoglobin level. Full blood counts will be measured monthly, as per usual clinical practice. Iron studies will be measured every 2 months, as usual clinical practice. Patients will receive a medical review by their nephrologists every 2 months, as per usual clinical practice. No other procedure will be undertaken and all other care (including blood tests) will be provided according to standard unit protocols. Figure 2 outlines the trial schedule.

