**Figure 2 F2:**
[figure not shown]
**Trial schedule (all tests are ordered as per routine clinical practice)**.

An individual patient's participation in the study will cease at the end of the 6 month study period. If, before this time, the patient experiences severe anaemia (<65 g/L), symptomatic anaemia (e.g. new onset or worsening shortness of breath or ischaemic chest pain attributable to the low haemoglobin) or the patient's attending physician believes that additional therapy is required (eg blood transfusion), they will be considered to have reached an end-point and will be withdrawn from study medication, but will still have blood counts measured monthly and followed for study outcomes. A patient's participation in the study will also cease if, during the course of the study, they complete PD therapy (eg renal transplantation or conversion to haemodialysis).

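### The in-study list of prohibited treatments omits intravenous iron and non-study oral iron, so elective use that acts directly on TSAT is not clearly barred or counted

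*Protocol article*

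**What the plan says.** All references are to the protocol article.

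- **Entry (Participants, exclusion 11).** Patients are excluded for any of five therapies: "Intravenous iron therapy, vitamin C therapy, melatonin treatment, androgen therapy or blood transfusion within the previous month".
- **During the study (Concurrent Treatments).** "Vitamin C supplementation, melatonin and androgen therapy are prohibited during the study period". Vitamin B and folic acid are allowed. Intravenous iron and non-study oral iron are not mentioned.
- **End-point rule (Blinding, repeated in the text under Figure 2).** Besides severe and symptomatic anaemia, a patient reaches an end-point if the "attending physician believes that additional therapy is required (eg blood transfusion") applies. Study medication then stops, but patients "will still have blood counts measured monthly and followed for study outcomes".
- **Background care (Procedures).** "all other care (including blood tests) will be provided according to standard unit protocols", and "Iron studies will be measured every 2 months, as usual clinical practice".
- **Primary outcome (Outcome measures; Primary Outcome Analyses).** The between-group difference in TSAT at 6 months, by analysis of covariance and intention to treat. For patients who withdraw early, the TSAT at withdrawal stands in for a final value, which the sentence calls haemoglobin.
- **Adverse Events.** Iron deficiency alone is not an adverse event.

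**The concern.** Intravenous iron is the co-treatment that acts most directly on the primary outcome. The Background reports that it gave better iron stores than oral iron in the group's own cross-over trial in PD patients. The protocol recognises its importance at entry but does not carry it into the in-study list.

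Treating physicians know the arm and see iron indices every 2 months. If intravenous iron were given more often in one arm, part of the month-6 TSAT difference would reflect that iron rather than the study drug. Two sites could also handle the same elective dose differently. One might call it an end-point and stop study medication; the other might carry on and treat the month-6 TSAT as an ordinary result.

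The Background itself lists "potential for co-intervention and observer biases" among the weaknesses of the earlier HIP study in haemodialysis patients.

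**Working it through.** **1. The text, side by side**

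| Exclusion 11 therapy | Prohibited in-study | Named in end-point rule |
|---|---|---|
| Vitamin C | yes | no |
| Melatonin | yes | no |
| Androgens | yes | no |
| Transfusion | no | yes |
| Intravenous iron | no | no |

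Intravenous iron is the only one of the five with no explicit in-study rule. Non-study oral iron has neither an in-study rule nor an entry rule. The end-point rule turns on the physician's view that more therapy is required and sets no TSAT or ferritin trigger. A dose judged necessary fits it. A top-up given under a unit protocol because an index is low, in a patient without symptoms, fits less clearly.

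**2. The plan's own sample size**

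Inputs (Sample size calculations): difference d = 7, SD = 8, alpha 0.05 (taken as two-sided), 22 per arm, 15% drop-out, 60 recruited.

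Method: two-sample t-test, noncentrality = d / (SD × √(2/n)), with 2n − 2 degrees of freedom.

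- n = 22: 7 / (8 × √(2/22)) = 7 / 2.412 = 2.90, power 80.9%. The stated 80% with 22 per arm is reproduced.
- Inflation: 44 / 0.85² = 60.9, against the stated 60.

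**3. How much dilution the design can absorb**

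After the planned drop-out, 30 × 0.85 = 25.5, taken as 26 per arm. No gain from baseline adjustment is assumed; ANCOVA would leave somewhat more room.

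| n per arm | Power at d = 7 | d giving 80% power | Slack (7 − that d) |
|---|---|---|---|
| 26 | 87.2% | 6.34 | 0.66 |
| 30 (no drop-out) | 91.5% | 5.885 | about 1.1 |

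**4. What would use up the slack**

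Shift in the TSAT difference = (excess proportion treated in one arm) × (TSAT gain per treated patient). The document gives neither quantity, so what follows is illustration only, with an assumed gain of 5 to 15 points and the excess in the control arm.

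The nearest rate in the document is from the earlier HIP study, where one of 37 patients left for "insufficient iron supplementation (n = 1"): 1/37 = 2.7% over 6 months. That is a haemodialysis figure and not a rate of intravenous iron use.

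| Excess | Gain | Shift | Power, 26/arm | Power, 30/arm |
|---|---|---|---|---|
| 2.7% | 5 | 0.14 | 85.9% | 90.5% |
| 2.7% | 10 | 0.27 | 84.5% | 89.3% |
| 2.7% | 15 | 0.41 | 83.0% | 88.1% |
| 10% | 5 | 0.50 | 81.9% | 87.2% |
| 10% | 10 | 1.00 | 75.6% | 81.5% |

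At a 10% excess, the gain needed to bring power to 80% is 0.66 / 0.10 = 6.6 points at 26 per arm and about 11 points at 30 per arm.

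**5. Direction**

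If HIP truly works and intravenous iron goes mainly to controls, the difference shrinks. If it goes mainly to the HIP arm, the difference grows. If there is no true effect, an imbalance either way creates a difference: at 26 per arm a shift of 0.5 points raises the two-sided rejection rate from 5% to 5.6%, and a shift of 1.0 point to 7.3%. The direction therefore depends on who is treated and why.

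**The case against.** **The end-point rule may already cover it.** Intravenous iron and transfusion are the two exclusion 11 therapies that a patient may clinically need, so leaving both off a flat prohibition is coherent. Transfusion is only an example in the rule, and the physician's judgement stands as an alternative to severe or symptomatic anaemia. This stands for rescue use. A reader might infer that intravenous iron is wholly unregulated after randomisation; the text does not support that.

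**Routine use is not shown.** A reader might infer that these units give maintenance intravenous iron. The 2-monthly infusions in the Background were a trial arm. The Background says guidelines favour oral iron first in PD, and the Discussion calls intravenous iron logistically difficult and costly. The statement on all other care can also be read as care apart from iron, the trial treatment. This stands against any claim of heavy use. It does not close the gap, because the Background also says oral iron fails to maintain stores in PD over the medium to long term.

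**The comparison with the earlier HIP study is imperfect.** That study was uncontrolled and non-randomised, whereas this trial has a concurrent randomised control. That stands. Randomisation does not, however, prevent unequal co-treatment afterwards.

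**An article condenses the protocol.** True, but this article prints a specific list of prohibited treatments, and the list as printed omits the treatment most relevant to TSAT.

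**Making rescue an end-point does not remove its effect.** Patients rescued and followed to month 6 still contribute a TSAT that includes the rescue iron. This stands and is dealt with in the fix.

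**Conclusion.** The point holds in limited form and is a cheap improvement. The prohibited list omits intravenous iron and non-study oral iron. Rescue intravenous iron is plausibly an end-point already; elective use for low indices is neither clearly barred nor clearly counted.

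The size cannot be derived, because the document gives no rate of in-study use and no TSAT response to it. Under the assumptions shown, the effect is small at a 2.7% excess (power at 26 per arm 83.0% to 85.9%, above the planned 80%) and moderate at 10% (81.9% to 75.6% for gains of 5 to 10 points).

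Two stronger readings should be resisted. One is that the trial is underpowered because of this; that needs assumed inputs. The other is that the only possible harm is dilution; that assumes intravenous iron follows poorer iron status in the arm that truly does worse. Unequal use driven by knowledge of the arm or by gastrointestinal intolerance could push the estimate either way.

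The carry-forward sentence is a secondary matter. It names the wrong variable and does not say whether patients off study medication but still followed contribute their month-6 TSAT.

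**What to change.** 1. **Concurrent Treatments:** add elective intravenous iron and non-study oral iron to the prohibited list.
2. **End-point rule (Blinding and the text under Figure 2):** give intravenous iron as a second example beside transfusion. Needed rescue is then never withheld but always counts as an end-point.
3. **Supportive analysis:** keep the intention-to-treat analysis as primary, and add one that uses the last TSAT before rescue for patients who received it.
4. **Primary Outcome Analyses (secondary correction):** replace haemoglobin with TSAT in the carry-forward sentence, and apply it only to patients with no month-6 TSAT. This agrees with the continued follow-up already promised.

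**Cost:** a few words in three places and one extra analysis; no additional patients or visits. Some patients given intravenous iron as usual care would stop study medication, which may itself weaken the contrast between arms. Month-6 TSAT in rescued patients would still include the rescue effect in the primary analysis, which is why item 3 is needed.
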